### Power analysis and sample size determination

2.4

A sample size power calculation was performed prior to the start of the study [33]. The power calculation serves as a lower-bound estimate of power if each patient has at least two measurements. Multiple observations per subject will increase the power and eliminate the impact of possible missing observations. With a significance level of 5%, a power of 90% and a Clinically Relevant Difference (CRD) of 1 x SD between groups A and B, at least 23 participants will be required in each group, with a total number of 46 participants. A total of 26 participants per group will be recruited to account for a 15% dropout, while retaining sufficient statistical power.

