### Outcome measures

2.9

The primary outcome is the change in the Saccadic Reaction Time (SRT), measured using the BulbiCAM visual field test [36]. SRT will be assessed at all measurement points throughout the study to evaluate both immediate and sustained effects of the vision rehabilitation training. Secondary outcomes include changes in occupational performance and satisfaction using the Canadian Occupational Performance Measure (COPM) [37,38], health-related quality of life (EQ-5D-5L) [39], Self-regulation Skills Interview [40], Brain Injury Associated Visual Impairment Impact Questionnaire (BIVI-IQ) [41], and a questionnaire on the impact of driving on daily life (IDDL). All will be evaluated at each measurement point. Additionally, changes in reading speed will be measured using the Norwegian version of the International Reading Speed Texts (IReST) [42] and visual functions will be assessed. In addition to these quantitative outcomes, qualitative data will be collected through semi-structured interviews to explore participants' experiences with vision loss, the impact of losing their driver's license on daily life and quality of life, and their expectations of vision rehabilitation before starting the home-based training and their perceptions of the vision rehabilitation after the eight weeks of training.

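### The 90% power is called a lower bound without condition, but this is assured only for a baseline-adjusted week-8 comparison, which the article does not specify; later visits cannot remove the effect of missing week-8 values

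*Protocol article*

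**What the plan says.** Protocol article, section 2.4 (power analysis), assumes a 5% significance level, "a power of 90% and a Clinically Relevant Difference (CRD) of 1 x SD between groups A and B", and concludes that "at least 23 participants will be required in each group, with a total number of 46 participants". It recruits 26 per group to allow for 15% dropout. Two statements accompany the figure:

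- On the status of the figure: "The power calculation serves as a lower-bound estimate of power if each patient has at least two measurements".
- On what repeated visits are expected to achieve: "Multiple observations per subject will increase the power and eliminate the impact of possible missing observations".

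Section 2.4 does not say which SD the difference is scaled by, and it gives no correlation between visits.

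Elsewhere in the article:

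- Section 2.9: "The primary outcome is the change in the Saccadic Reaction Time (SRT"), assessed at every measurement point.
- Section 2.8: intervention effects are tested by repeated-measures ANOVA. The stratification factors are to be accounted for, and age and sex considered. Baseline SRT is neither named nor excluded as a covariate.
- Section 2.6: the delayed group is a waiting-list control for eight weeks and then receives the same training.
- Sections 2.8 and 2.11: dropouts are left out of the analysis (and replaced). Participants classed as withdrawals are kept, using last observation carried forward.

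**The concern.** A power figure is a lower bound only if the planned analysis can never be less precise than the one used for the calculation. The calculation treats each patient as giving one value. A change score uses two values and carries the measurement variation of both. When the two are only weakly correlated, subtracting the baseline adds noise, so a second measurement can lower power.

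The statement about multiple observations has a separate problem. Training starts in group B after week 8, so no untreated arm exists at any later visit. Later data do not replicate the treated-versus-untreated comparison and cannot stand in fully for a missing week-8 value.

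At stake is whether 90% is truly a minimum in a trial of 46 to 52 people, and whether precision available from a baseline already measured in everyone is left unused.

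**Working it through.** **Inputs.** From section 2.4: alpha 5%, power 90%, difference 1 SD, 23 per group. Two-sided testing is inferred, since a one-sided normal calculation gives 18 per group. The baseline to week-8 correlation of SRT, rho, is not in the document and is treated as an assumption over a range.

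**Step 1: the plan's own figure.** For a two-sample t-test with n per group and standardised difference d, the noncentrality is d × sqrt(n/2) on 2n − 2 degrees of freedom. With d = 1, n = 22 gives power 0.8997 and n = 23 gives 0.912. The stated 23 per group reproduces.

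**Step 2: change score at week 8, 1 SD read as the SD of one measurement.** With weeks 0 and 8 only, the group-by-time test in repeated-measures ANOVA is the t-test on change.

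- SD of change = SD × sqrt(2(1 − rho)), so d = 1/sqrt(2(1 − rho)).
- This equals 1 exactly at rho = 0.5 and is smaller below it. At rho = 0.3, sqrt(2 × 0.7) = 1.183 and d = 0.845.

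**Step 3: the same comparison adjusted for baseline SRT.** Residual SD = SD × sqrt(1 − rho²), so d = 1/sqrt(1 − rho²), with one further degree of freedom used.

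| rho | Change score, power at 23 per group | n per group for 90% | Baseline-adjusted, power at 23 per group |
|---|---|---|---|
| 0 | 0.650 | 44 | 0.912 |
| 0.2 | 0.746 | 35 | 0.923 |
| 0.3 | 0.800 | 31 | 0.935 |
| 0.4 | 0.857 | 27 | 0.951 |
| 0.5 | 0.912 | 23 | 0.969 |
| 0.7 | 0.990 | 14 | 0.996 |

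The adjusted column ignores chance baseline imbalance. A simulation of 6,000 trials, which includes it, gave 0.904, 0.930, 0.948 and 0.966 at rho 0, 0.3, 0.4 and 0.5. Using six model degrees of freedom instead of one leaves the formula value at 0.911 when rho = 0. Adjusted power therefore stays at or above 0.90 throughout.

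**Step 4: sensitivity to the number analysed (change score).** With 22 per group (26 × 0.85 = 22.1): 0.782 at rho 0.3, 0.841 at 0.4, 0.900 at 0.5. With all 26: 0.848 at 0.3 and 0.898 at 0.4.

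**Step 5: 1 SD read as the SD of change.** Then d = 1 whatever rho is, and power is 0.912. Both controlled measurements are already used, so the figure is exact for the change-score comparison. Baseline adjustment still helps: the variance ratio to the change score is (1 − rho²)/(2(1 − rho)) = (1 + rho)/2, which is 0.75 at rho 0.5.

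**Step 6: do later visits add power?** Only under a model that borrows across time. Assume equal correlation between visits, a linear time trend common to both groups, common end-of-training and 12-week effects, and visits at weeks 0, 8, 20 (A) and 0, 8, 16, 28 (B). Generalised least squares then gives about 8% lower variance for the end-of-training effect than weeks 0 and 8 alone. Power rises from 0.80 to 0.83 at rho 0.3, from 0.857 to 0.885 at 0.4, and from 0.912 to 0.934 at 0.5. With a free mean for each group and visit, and complete data, the gain is nil.

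**Step 7: missing values.** A dropout contributes nothing. A withdrawal before week 8 has the baseline value carried forward, which sets that patient's change to zero. Neither rule uses later visits to recover the week-8 value, and both affect the estimate.

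**The case against.** The strongest reply is that the outcome is a change, so 1 SD may well mean the SD of change; two measurements are the minimum needed to form one. On that reading there is no shortfall at any rho. This stands as a possible reading. The lower-bound wording fits a single-measurement SD at least as well, and the document settles neither. Even so, the reply rescues the 90%, not the description of it as a lower bound for a change-score analysis.

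Second, a condensed article may leave the covariate list to a fuller plan, so the absence of baseline SRT is not an error in itself. That stands. A reader might infer that the primary analysis is definitely unadjusted; the article does not say so. The point concerns a claim that section 2.4 makes outright and that depends on this choice.

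Third, section 2.8 does not restrict the ANOVA to weeks 0 and 8, and group B's move from waiting to training carries within-patient information. That also stands: it would be too strong to say that later visits add nothing. Step 6 shows a modest gain, which rests on an assumed time trend.

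A reader might also infer that the trial is underpowered. The documents do not support that: rho is not given, and at 0.5 or above the stated power is met on either reading of the SD.

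**Conclusion.** The concern holds in conditional form.

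- The unconditional lower-bound statement is not assured for the outcome and analysis described. On the single-measurement SD, the week-8 change-score comparison has 80% power at rho 0.3 and 86% at 0.4 with 23 per group, and meets the stated level only from about rho 0.5. On the SD of change, 0.912 is exact for that comparison rather than a floor.
- The statement that repeated observations eliminate the impact of missing values is wrong on the article's own design and handling rules. The statement that they increase power holds for the treated-versus-untreated contrast only under added assumptions about the time trend.
- Baseline adjustment makes the lower-bound statement true under either reading of the SD.

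The figures assume two-sided testing, equal variances at the two visits and a range for rho. No bias and no error in the figure of 23 per group are shown. The change should be made because it costs almost nothing and protects precision in a small trial.

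**What to change.** 1. In section 2.8, define the primary analysis as the week-8 comparison of SRT between groups A and B, adjusted for baseline SRT and the two stratification factors.
2. In section 2.4, state whether 1 × SD is the SD of a single SRT measurement or of the change.
3. In section 2.4, limit the lower-bound statement to that baseline-adjusted week-8 comparison.
4. In section 2.4, remove the claim that multiple observations eliminate the impact of missing data, and make any power gain from later visits conditional on the model used.

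The cost is a few sentences. Baseline SRT is already scheduled for every participant, so no data, visits or participants are added.

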**Methods:**

This study is an open, randomized controlled trial (RCT) with delayed-start design. Stroke survivors aged 20-85 years (N = 52) will be recruited from a vision rehabilitation clinic in Norway and randomized into two arms: A) immediate start of eight-week home-based vision rehabilitation intervention and B) delayed start (eight weeks) of the same eight-week vision rehabilitation intervention. A quantitative and qualitative approach will be applied to assess changes in functional vision after eight weeks of vision rehabilitation, and at twelve weeks post-intervention in both groups. The quantitative analysis includes descriptive statistics, plots and inferential statistics of effects. In addition, ten participants will be recruited for qualitative individual interviews before and after the eight-week intervention to explore experiences of living with VFL and participating in the intervention. For the qualitative analysis, we will apply thematic analysis.

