### Study design

2.1

The study will be performed as an open controlled and randomized stratified trial with a delayed-start design (Fig. 1). Participants will be randomized (1:1) to either an immediate (group A) or a delayed (group B) eight-week intervention. Both groups will perform objective and subjective assessments such as visual function assessments and questionnaires. Assessments will be performed at baseline, immediately after the intervention, and 12 weeks after the intervention. Participants assigned to the delayed group will begin the intervention with an eight-week delay.

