### Discontinuation/withdrawal

2.11

A participant may discontinue the study or withdraw their consent at any time without concerns about their future treatment or care. If a participant does not attend an agreed assessment/meeting, the researcher should try to motivate the participant to continue. If a participant decides not to continue for reasons documented as not being related to the research question, they will be classified as “dropouts” and replaced by a new participant. Reasons for discontinuation will be discussed in a dialogue between the lead researcher and the participant and subsequently evaluated by the research team in relation to the research questions. The dropouts will not be included in the statistical analysis. Participants who discontinue or exit the study for reasons related to the study question or to the study procedure or equipment will be classified as “patient withdrawals”. These will not be replaced, but they will be included in the analysis using a last observation-carried-forward procedure.

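### 26 per group does not absorb a 15% dropout down to the plan's own minimum of 23; it absorbs about 11.5%, and section 2.4 is not reconciled with the replacement rule in 2.11

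*Protocol article*

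**What the plan says.** Section 2.4 (Power analysis and sample size determination) takes a 5% significance level, 90% power and a "Clinically Relevant Difference (CRD) of 1 x SD between groups A and B". From these it concludes that "at least 23 participants will be required in each group, with a total number of 46 participants". It then adds the dropout margin: "A total of 26 participants per group will be recruited to account for a 15% dropout, while retaining sufficient statistical power". The abstract gives the matching total: "Stroke survivors aged 20-85 years (N = 52").

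Section 2.11 (Discontinuation/withdrawal) treats two kinds of exit differently. Participants who leave for reasons documented as unrelated to the research question are classed as dropouts "and replaced by a new participant", and they are left out of the analysis; section 2.8 (Statistical methods) repeats that exclusion. Those who leave for reasons connected with the study question, procedure or equipment are classed as withdrawals. They are not replaced, but stay in the analysis with their last observation carried forward.

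**The concern.** A reader takes section 2.4 to mean that the trial can lose 15% of each group and still have the 23 it says it needs. The three printed numbers (23, 26 and 15%) do not fit together in that way.

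There is also an overlap between sections. If 26 already includes a margin for dropout, it is unclear why dropouts are replaced as well. If they are replaced, it is unclear what the margin is for. The article leaves open whether 52 is the final number randomised or whether replacements come on top of it. What is at stake is the accuracy of the sample-size statement and a definite recruitment total, not the trial's ability to detect the planned difference.

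**Working it through.** **Inputs.** All are from section 2.4 unless noted: significance level 5%; power 90%; standardised difference 1.0; 1:1 allocation (section 2.1, Study design); minimum 23 per group, 46 in total; recruited 26 per group, with 52 in total from the abstract; dropout 15%. Sidedness is not stated. I assume a two-sided test, because that reproduces the plan's figure; a one-sided normal approximation would give 18 per group.

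**Step 1: reproduce the base size.** Solving the two-sample t-test (noncentral t) for d = 1, two-sided 5% and 90% power gives 22.02 per group, rounded up to 23. This matches the plan, so the assumptions and the base size are not in question.

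**Step 2: apply the stated dropout to the recruited number.**
- Per group: 26 x (1 - 0.15) = 22.1, against 23 required.
- In total: 52 x 0.85 = 44.2, against 46 required.

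**Step 3: find the loss that 26 does cover.** 26 - 23 = 3 per group, and 3/26 = 11.5%.

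**Step 4: see how 26 could have arisen.**
- Dividing the printed minimum by the retention rate: 23/0.85 = 27.06, which is above 26.
- Multiplying it up: 23 x 1.15 = 26.45, which gives 26 only if rounded down.
- Dividing the unrounded requirement: 22.02/0.85 = 25.9, which rounds up to 26.

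The article does not say which route was used.

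**Step 5: power at the relevant sizes** (two-sided two-sample t-test, difference 1 SD).

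| Per group | Power |
|---|---|
| 22 | 89.97% |
| 23 | 91.2% |
| 26 | 94.2% |

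Going from 23 to 22 costs about 1.3 percentage points and leaves power 0.03 points below the 90% target.

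**Step 6: set 2.4 beside 2.11.** Under 2.11 a dropout is replaced and a withdrawal stays in the count by carrying the last value forward. If both rules operate as written, the number analysed stays near 26 per group and 22 is not reached. If replacement does not operate, 2.4 applies alone and a 15% loss gives the 22.1 of step 2. The article does not say how the two sections relate.

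**The case against.** The strongest defence is that 26 may be correct. Dividing the unrounded requirement of 22.02 by 0.85 gives 25.9, hence 26 per group. On that route the recruited number is properly inflated, and the mismatch comes only from rounding 23 and 26 separately. In addition, the sentence promises sufficient power, not 23 per group after losses, and power of 89.97% meets that promise for any practical purpose. Section 2.4 also describes its calculation as a lower bound, because repeated measurements should add power.

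Most of this stands. It means that 26 cannot be called a wrong recruitment target, and that the promise about power is not materially false. It does not rescue the wording: the article prints 23 as the minimum, and a 15% loss from 26 falls below it.

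A reader might infer that the trial will be underpowered, or that it must recruit more. The documents do not support either reading. Power at 22 per group is about 90%, and the replacement rule, if applied, prevents 22 from occurring.

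A reader might also infer that the margin and the replacement rule contradict each other outright, so that replacement should be deleted. That goes too far. Replacement covers only exits unrelated to the research question, and a withdrawal kept by carrying a baseline value forward adds no post-treatment information, so holding some margin as well can be a cautious choice. Deleting replacement while dropouts remain excluded from the analysis would make the shortfall possible. What remains is that the article does not explain how the two fit together.

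**Conclusion.** The point holds as a misstated planning figure of minor consequence. With 23 as the printed minimum, 26 per group tolerates 3 losses per group (11.5%), not 15%; a 15% loss leaves about 22 per group, or 44 in total against 46. No material loss of power follows: 89.97% at 22 against 91.2% at 23. These power figures assume a two-sided two-sample t-test with a difference of exactly 1 SD, and no gain from repeated measurements. The figure of 22 also assumes that lost participants are neither replaced nor retained, which is not what section 2.11 provides. Separately, sections 2.4 and 2.11 leave open how dropouts are handled for recruitment and whether 52 is a ceiling.

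**What to change.** 1. In section 2.4, replace the dropout sentence with wording such as: *26 per group allows for about 11% loss (3 per group) while keeping 23; a 15% loss would leave about 22 per group, with power of about 90%.*
2. In section 2.4 or 2.11, add a clause saying whether the recruitment margin or replacement deals with dropouts (or what each is meant to cover), and whether N = 52 includes replacements. Either arrangement can be made consistent, and the choice belongs to the trial team.

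The cost is two or three sentences and a slightly less favourable stated allowance. The design and analysis do not change, and no additional participants are needed.

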### Randomization, stratification and blinding

2.5

“Time since stroke onset” and “Extent of visual field loss” are used as stratification factors. The first factor is divided into “< 6 months”, “6-12 months” and “> 12 months”, whereas the second is devided into complete- and partial hemianopia (Fig. 2). We define complete hemianopia as loss of an entire hemifield, while partial hemianopia refers to incomplete loss with preserved areas within the affected hemifield.

**Fig. 2 fig2:**
[figure not shown]
Study randomization and stratification factors.

Within each strata the participants will be randomly allocated (1:1) to either immediate or delayed intervention at baseline. Allocation will be concealed in sealed envelopes prepared by an independent researcher. The main researcher will not gain access to the pre-randomization list.

Due to the nature of the intervention, neither participants nor the main researcher ([name]) can be blinded after allocation. Other project group members and researchers will be blinded to the treatment allocation.

### The study intervention

2.6

After the baseline assessment, including an optometric assessment and completion of questionnaires (Table 1), participants will be randomly allocated to one of two groups (Fig. 1).

**Table 1 tbl1:** Overview of data assessment schedule for SUB-STUDY I, II and III.

Sub-study	Name of test	Test information/measure of	Assessor	Time of assessment (week)				
				0	8	16	20	28^a^
**Background and clinical information**								
I	Anamnesis	Demographics	Researcher/participant	X				
I	MoCA	Cognitive functioning	Researcher	X				
I	NIHSS	Stroke severity	From patient record	X				
I	Heart cancellation	Visual attention	Researcher	X				
I	Barthel ADL-index	ADL-functions	Participant	X	X	X	X	X
**Self-reported questionnaires/interview**								
I&II	FSS	Fatigue severity	Participant	X	X	X	X	X
I&II	SRSI	Self-regulation, motivation	Researcher	X	X	X	X	X
I&II	BIVI-IQ	Visual impairment impact	Participant	X	X	X	X	X
I&II	EQ-5D-5L	HQOL	Participant	X	X	X	X	X
I&II	COPM	Occupational performance	Researcher	X	X	X	X	X
I&II	IDDL	Impact of driving on daily life	Participant	X	X	X	X	X
**Optometric vision assessments**								
I	LogMAR	Visual acuity	Optometrist/researcher	X	X	X	X	X
I	Cover-test	Heterophoria	Optometrist/researcher	X	X^a^			
I	MARS-test	Contrast sensitivity	Optometrist/researcher	X	X	X	X	X
I	Near point of convergence	Convergence	Optometrist/researcher	X	X	X	X	X
I	HRR	Colour vision	Optometrist/researcher	X	X^a^			
I	TNO	Stereoacuity	Optometrist/researcher	X	X	X	X	X
**Visual Field Assessments**								
I&II	Esterman	Binocular VF	Researcher	X	X	X	X	X
**Primary outcome**								
I&II	BCAM VFT	Visual field test	Researcher	X	X	X	X	X
**Secondary outcome**								
I&II	IReST	Reading speed	Researcher	X	X	X	X	X
I&II	BCAM Saccade test	Saccade latency, peak velocity, accuracy	Researcher	X	X	X	X	X
**Qualitative method**								
III	Individual interviews	Experiences	Researcher/participant	X	X	X		

a Only for group B.

Immediate group: Participants in the immediate group will receive the intervention immediately. The intervention consists of eight weeks of home-based training exercises for visual scanning, visual search and eye movements, aimed at developing compensatory strategies for visual field loss. The training will include both a licensed online vision training program (Vision Builder) [34] and manual exercises. Participants will be instructed to complete 20 min of vision training daily, with a minimum recommended total training of 20 h over the eight-week period.

Adherence, motivation and perceived visual function will be closely monitored throughout the intervention. Each participant will receive a short weekly telephone check-in with open-ended questions, and they will be asked to maintain a training diary. Adherence will be categorized as “good”, defined as performing vision training 5–7 days/week, as “partial”, performing vision training 1–3 days/week, or “none”, as no training. Active measures will be taken to promote compliance. Visual function assessments and questionnaires will be repeated immediately after the intervention in week eight, with a final follow-up assessment conducted 12 weeks after completion. Additionally, participants will evaluate the acceptability and relevance of the training through a survey and qualitative interviews.

Delayed group: Participants in the delayed-start group will serve as a waiting-list control group and receive standard care for the first eight weeks. After the waiting-list control period and corresponding assessments, they will receive the same vision rehabilitation intervention as described for the immediate group.

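### Exactly 20 min daily for eight weeks totals 18.7 h, below the recommended 20 h minimum, and the adherence scale has no category for 4 days a week

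*Protocol article*

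**What the plan says.** All the relevant text is in section 2.6 of the protocol article (The study intervention), in the description of the immediate group after Table 1.

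- **Duration.** "The intervention consists of eight weeks of home-based training exercises for visual scanning, visual search and eye movements".
- **Amount.** Participants are asked for "20 min of vision training daily, with a minimum recommended total training of 20 h over the eight-week period". The daily instruction and the total stand in one sentence.
- **Adherence.** The top category, good, is "defined as performing vision training 5–7 days/week". The other two are partial, "performing vision training 1–3 days/week, or “none”, as no training".
- **Recording.** Each participant has a short weekly telephone call, and "they will be asked to maintain a training diary".

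The delayed group later receives the same intervention, so the same figures apply to both arms (26 per group, 52 in all, section 2.4). No other section gives a different session length, training period or adherence rule.

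**The concern.** Two stated rules do not work when applied as written.

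First, the daily instruction and the recommended minimum disagree. Someone who does exactly what the instruction says, every day for eight weeks, does not reach the minimum.

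Second, the adherence scale jumps from 3 to 5 days a week. It is also not tied to the minimum, since neither minutes per day nor total hours enter the grading.

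What is at stake is the account of how much training was delivered. The Discussion says that the findings will bear mainly on feasibility. It names variable adherence as a limitation that may affect fidelity, and says that this must be weighed when results are interpreted. The three categories are the only classification of adherence that the article defines. If they have a gap, and if the top category can sit below the stated minimum, the report cannot say cleanly who received the intended amount.

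The gap at 4 days a week would have to be filled ad hoc. The main researcher, who conducts all data collection (section 2.7.1), is not blinded after allocation (section 2.5). That is a reason to settle the rule in advance.

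**Working it through.** **Inputs, all from section 2.6**

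- Session: 20 min, daily (7 days a week)
- Period: 8 weeks = 8 × 7 = 56 days
- Recommended minimum: 20 h = 20 × 60 = 1200 min
- Categories: good 5–7 days a week, partial 1–3, none 0

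**Step 1: try to reproduce the 20 h.** Total = 20 min × 56 days = 1120 min; 1120 / 60 = 18.67 h. The stated figure is not reproduced. The shortfall is 1200 − 1120 = 80 min, and 80 / 1200 = 6.7%, so full compliance gives 93.3% of the minimum. Counting the period differently does not rescue it: seven weeks of daily training give 7 × 7 × 20 / 60 = 16.3 h, and only a ninth week (9 × 7 × 20 / 60 = 21.0 h) passes 20 h. The plan says eight.

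**Step 2: set the adherence scale against the minimum.** Assume 20 min on each training day. This assumption is needed because the categories count days and not minutes.

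Hours = 20 × days per week × 8 / 60

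| Days per week | Minutes | Hours | Share of 20 h | Category |
|---|---|---|---|---|
| 7 | 1120 | 18.67 | 93.3% | good |
| 6 | 960 | 16.00 | 80.0% | good |
| 5 | 800 | 13.33 | 66.7% | good |
| 4 | 640 | 10.67 | 53.3% | not assigned |
| 3 | 480 | 8.00 | 40.0% | partial |
| 2 | 320 | 5.33 | 26.7% | partial |
| 1 | 160 | 2.67 | 13.3% | partial |
| 0 | 0 | 0 | 0% | none |

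On that assumption the whole good category, 13.3 to 18.7 h, lies below the stated minimum. Its lowest pattern falls short by 20 − 13.33 = 6.67 h, one third of the minimum.

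**Step 3: relax the assumption.** With longer sessions, a participant rated good can reach 20 h. With sessions shorter than 20 min on 5 days a week, a participant rated good has less than 13.3 h. The label alone does not distinguish these cases.

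**Step 4: the gap.** The listed values are 0, 1–3 and 5–7. Of the eight possible whole-day counts in a week, only 4 has no category, whatever the session length.

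**The case against.** The best case on the other side has four parts.

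**The minimum can still be met.** A reader might infer that participants cannot reach 20 h, or that nobody who complies can. The article does not support that. It does not call 20 min a maximum, so someone who trains somewhat longer satisfies both statements. The 20 h is a recommendation, not an eligibility or per-protocol threshold. This stands, and it limits the point to exact adherence to the daily instruction. It does not remove the conflict between the two figures.

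**Frequency and total may be graded separately by design.** That is a legitimate choice, and good need not coincide with a total below the minimum. The 13.3 h figure depends on 20 min per training day. This also stands, so the claim is only that the two can coincide.

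**The underlying record is not lost.** A reader might infer that exposure will be misclassified, or that people training 4 days a week will drop out of the results. The first uses the wrong word, since such a participant is unclassified. The second has no basis: section 2.8 names no analysis that uses the categories, and the diary and weekly calls exist beside them. The article does not say, however, that the diary records minutes, so it cannot be assumed to supply total hours.

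**An article condenses the full protocol.** That would answer a complaint about missing detail. It does not answer two stated figures that disagree, or a stated scale that leaves out one value. A later analysis plan could add an adherence analysis, but it would not change the instruction given to participants.

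**Conclusion.** The point holds in a limited form. Following the daily instruction exactly yields 18.7 h against a recommended minimum of 20 h, a gap of 80 min or 6.7%. The adherence scale leaves 4 days a week without a category. Its top category can coincide with a total below the minimum: 13.3 to 18.7 h, on the assumption of 20 min per training day. The 18.7 h figure and the gap at 4 days need no assumption beyond the text.

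The harm is to the description of delivered exposure and fidelity, and to any adherence or dose-response analysis added later. A reader might go further and infer that the main result is compromised. It is not: the randomised comparison of the primary outcome uses neither the 20 h figure nor the adherence categories, and neither enters the sample size calculation in section 2.4.

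The correction is worth making because adherence matters to a trial that expects to speak mainly to feasibility, and because it costs almost nothing.

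**What to change.** 1. The sponsor should reconcile three statements in section 2.6: the daily instruction, the recommended 20 h and the definition of good adherence. This review takes no view on which is right. The information given to participants should then carry the same figures.
2. Make the adherence categories exhaustive, so that 4 days a week falls in a named category, and fix that rule before outcomes are seen.
3. Report diary training days beside the categories, and minutes as well if the diary records them. This is optional, but it shows delivered exposure without relying on the labels.

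The cost is rewording one part of section 2.6 and checking what the diary form captures. No change to the randomisation, sample size, assessment schedule or primary analysis is needed.
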